Therefore, there is a discrepancy between treating and not treating PFF. There are authors who conclude that it is not necessary, since the natural evolution of the foot is that the MLA begins to form at 3–4 years of age and ends at 10 years of age [26,27]. A recent meta-analysis [30] concludes that, due to the normal development of the foot, treatments should be ruled out unless there are symptoms such as pain, limited function or reduced quality of life. However, other authors recommend early treatment, based on the fact that flat feet persist in 23% of adults and may be associated with Achilles tendinopathy, plantar fasciopathy, tibial posterior tendinopathy, hallux rigidus, chondromalacia patellae or patello-femoral pain syndrome [1,2,7,13,20]. Based on these latest data, it would be unethical to leave these types of feet untreated. Additionally, a recent systematic review [24] demonstrated that FO are beneficial, with evidence regarding efficacy in treating signs and symptoms.

Therefore, since PFF is a very common syndrome which, if left untreated, could cause problems in the long term and there is no consensus on the treatment protocol, it is necessary to investigate the effectiveness of FO in terms of improvement of the signs and symptoms, including the prevention of pathologies or injuries and the improvement of the quality of life. Sagat, P et al. have shown that children with flat feet presented poor performance in certain physical tasks, in contrast to a control group with neutral feet [31]. In addition, since it is a subject of great interest for researchers, health professionals and parents, it is necessary to carry out an investigation to assess the effectiveness of FO, with a standardized diagnostic protocol with validated tests in a larger sample size than previously published studies and with a longer-term follow-up. Furthermore, as the authors Zhang J. et al. pointed out, early identification of PFF is necessary; thus an intervention plays a crucial role in enhancing the outlook. Also, there is an absence of consistent quantitative standards for diagnosing flexible flatfoot [32].

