
### 2.5. Blinding and Monitoring

Participants and their parents/guardians will be blinded as to which group they are allocated to and will not see the other group.

An initial assessment will be made, these same measurements will be repeated 3 times throughout the duration of the study. In total we will obtain 4 measurements for statistical analysis.

The second measurement will be a month of treatment; in addition, in this visit we will assess the state of the FO and verify that the exercises are going well. We will ask about the FO, if any pain has appeared that was not there before, any blisters or reddened areas. In the event that the adaptation to the FO has not been good, we will make the necessary adjustments to the FO, such as lowering the MLA. If any subject needs their FO to be modified, they will be called by telephone after 2 weeks to see the evolution; in the event that it has not improved, it will be cited to re-evaluate the FO.

To corroborate that the execution of the exercises is good, we will ask the participant to repeat them, and in case there is an exercise that is not being performed correctly, we will explain it again.

The third assessment will be in the middle of the treatment/study period, that is, at 6 months. At this stage, all the initial measurements/assessments will be conducted again, as well as the last one at 12 months.

The estimated time for the measurement assessments is one hour for the 1st visit and 30 min for the rest of the visits.

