### 2.7. Statistical Analysis

The description of data will be calculated using the percentages and frequencies of the qualitative variables and for the quantitative variables, the standard deviation and the mean. In addition, in case of presenting high deviations, the measures of central tendency would be calculated, as is the case of the mean, median or mode. All this will be carried out in frequency distribution tables of different categories, using SPSS (IBM SPSS Statistics: V.28, USA).

It is intended to compare the dependent variables with the independent ones. The Kolgorov–Smirnof test (the adjustment to the normal of the distribution) will be used to check the normality of the quantitative variables; in the event that they follow a normal distribution, the following techniques would be used: linear regression or Pearson correlation for the comparison of quantitative variables, chi-square (X^2^) to compare qualitative variables and Student’s *t* or ANOVA to compare qualitative with quantitative variables. In the event that they do not conform to the normal, it will be calculated according to the case; the Wilcoxon test, the Kruskal–Wallis test, and the Mann–Whitney test.

To determine that the supposed differences between control group and experimental group are not due to a random error, but to a real difference, in the bivariate analysis a hypothesis test will be carried out. The significance level of p shall be 0.05.

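### Section 2.7 fixes an unadjusted bivariate test for the group comparison, leaving out baseline and age and giving no rule for using the three follow-up visits, at a cost in precision

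*Protocol article*

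**What the plan says.** Section 2.5 sets out the measurements: "In total we will obtain 4 measurements for statistical analysis". The first is the initial assessment. Of the next it says "The second measurement will be a month of treatment". The third is at 6 months, where "all the initial measurements/assessments will be conducted again, as well as the last one at 12 months". That makes one baseline and three follow-up values per child. Section 2.4.2 lists age, in months, among the variables collected.

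Section 2.7 then fixes the analysis. A Kolmogorov-Smirnov test "will be used to check the normality of the quantitative variables; in the event that they follow a normal distribution, the following techniques would be" Student's t "or ANOVA to compare qualitative with quantitative variables", with chi-square for pairs of qualitative variables and linear regression or Pearson correlation for pairs of quantitative ones. Otherwise: "In the event that they do not conform to the normal, it will be calculated according to the case", with Wilcoxon, Kruskal-Wallis and Mann-Whitney named. The control-versus-experimental difference is then judged as follows: "in the bivariate analysis a hypothesis test will be carried out", at 0.05.

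The introduction reports the view of some authors that "the MLA begins to form at 3–4 years of age and ends at 10 years of age". Section 2.2 enrols children aged 3 to 12.

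**The concern.** A bivariate test has two variables, here group and outcome, so neither the child's baseline value nor age has a place in it. Regression could carry them, but section 2.7 lists it only for relating one quantitative variable to another, not for the group effect. By the article's own account the arch is still forming in most of the enrolled age range. Age and baseline should therefore explain a good part of the variation in the follow-up values, and both are already collected.

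The section also gives no rule for turning three follow-up visits into one answer. If each visit is tested at 0.05, there are three chances to declare a difference. Finally, the Kolmogorov-Smirnov check lets the data choose the method, and with it the quantity being estimated, variable by variable.

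**Working it through.** **1. The plan's own sample size.** Section 2.6 gives a difference of 2, SD 1, 80% power, 0.05, and 64 per group. The normal-approximation formula is n per group = 2(1.96 + 0.84)² × (SD/difference)².

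- As printed (2 and 1): 2 × 7.85 × 0.25 = 3.9, so 4 per group (6 by the exact t-test). This does not give 64.
- With a standardised difference of 0.5: 2 × 7.85 × 4 = 62.8, so 63 (63.8, so 64, by the exact t-test; power at 64 is 80.1%).

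The stated 64 therefore fits a 0.5 SD effect and one unadjusted two-sample t-test on one value per child. I use 0.5 SD below as an assumption for that reason. The mismatch in section 2.6 is a separate matter.

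**2. Completers.** Section 2.6 enrols 84 per group and allows for 30% loss: 84 × 0.70 = 58.8, about 59 per group.

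**3. Power with and without baseline.** Adjusting for a baseline that correlates r with the outcome multiplies the residual variance by 1 − r², so the effective standardised difference is 0.5/√(1 − r²). The article gives no r, so I show a range. Two-sided t-test power at 0.05:

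| r (assumed) | 1 − r² | Effective difference | Power, 59 per group | Power, 64 per group |
|---|---|---|---|---|
| unadjusted | 1.00 | 0.500 | 76.8% | 80.1% |
| 0.3 | 0.91 | 0.524 | 80.6% | 83.7% |
| 0.5 | 0.75 | 0.577 | 87.5% | 90.0% |
| 0.7 | 0.51 | 0.700 | 96.5% | 97.6% |

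This counts baseline only. The further gain from age is not quantified, because the article gives nothing from which to size it.

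**4. Testing each follow-up visit at 0.05.** With no true effect, the three visit-wise test statistics are correlated at the within-child correlation ρ. The chance that at least one exceeds 1.96 in absolute value is:

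| ρ (assumed) | P(at least one false positive) |
|---|---|
| 0.3 | 13.6% |
| 0.5 | 12.5% |
| 0.7 | 10.9% |
| 0.8 | 9.8% |

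One pre-named visit would hold 5%.

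**5. The normality switch.** Null trials with 64 per group were simulated, choosing t or Mann-Whitney by a Lilliefors-corrected Kolmogorov-Smirnov test. Type I error was 4.9% for normal data, 4.9% for skewed data and 4.4% for a rounded score resembling FPI, so the switch did not inflate error. The rounded score went to the rank test in every simulated trial. For integer scores, then, the switch could in practice settle the method in advance, in favour of one that does not adjust for baseline.

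**The case against.** Much can be said for the plan. Leaving baseline and age out of a randomised comparison does not bias it, and a test at a single visit holds its 5% level. The sample size is consistent with exactly that use: one value per child, one two-sample test. The choice of covariates is partly a matter of preference. The power gain also depends on assumptions. Section 2.2 restricts baseline on several outcomes (FPI, navicular drop, RCSP), which tends to weaken the baseline-outcome correlation, and at r = 0.3 the gain is under four percentage points. At the printed 2 and 1, power would be close to 100% with or without adjustment.

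These points stand, and they limit the size of the finding. They do not remove it: the article affirmatively states a bivariate group test, and an analysis plan that adjusted for baseline would have to replace that statement, not just fill it in.

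Four stronger readings are tempting but not supported:

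- A reader might infer that all visits will be stacked as if they came from different children, which would inflate error well beyond the figures above. No section proposes this.
- A reader might infer that none of the listed tests can handle repeated measurements. Wilcoxon may mean the paired signed-rank test, and ANOVA is not specified further, so a repeated-measures form is not excluded. A paired test within each arm would still not answer the between-group question.
- A reader might infer that children without a final value are simply dropped. Section 2.7 is silent on missing values, section 2.6 uses the 30% only for sizing, and a separate analysis plan commonly settles the matter.
- A reader might infer that the normality check raises the false-positive rate. The simulation does not show that.

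**Conclusion.** The point holds as a matter of precision and of an unspecified visit rule, not of bias. As stated, the group comparison sets aside baseline and age, both already collected, and does not say which follow-up visit counts.

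Under the assumed 0.5 SD effect with 59 completers per group, the stated test falls short of the planned 80% power, at 77%. Baseline adjustment gives 81% to 96.5% over assumed correlations of 0.3 to 0.7. If every follow-up visit is tested at 0.05, the false-positive chance is about 10% to 14% over assumed within-child correlations of 0.8 to 0.3; that figure applies only if the analysis is done visit by visit. The correlations and the 0.5 SD are assumptions, since the article supplies neither. The change should be made, but the trial's validity does not depend on it.

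**What to change.** In section 2.7, for quantitative outcomes, replace the bivariate group test with a comparison adjusted for the baseline value and age in months, at one visit named in advance (for example the final one, which section 2.5 puts at 12 months). Either ANCOVA at that visit or a mixed model for repeated measures on all three follow-up visits would serve. Report the adjusted group difference with its 95% confidence interval, and label the other visits secondary.

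Remove the Kolmogorov-Smirnov test as the selector of method. Check residuals after fitting, and keep a rank test, if wanted, as a sensitivity analysis.

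The cost is a revised paragraph and slightly more analysis work. No new data or visits are needed.

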### 2.6. Sample Size

The calculation of the sample size has been carried out with the data analysis program EPIDAT https://www.sergas.es/Saude-publica/EPIDAT?language=es (accessed on 4 August 2023). For the calculation, a clinical variation of 2 and a standard deviation of 1 have been considered. A statistical power of 80% and a significance level of *p* < 0.05; 95% confidence level. The minimum size would be a sample of 128 subjects (64 in each group randomly distributed). Considering that the loss rate could be 30%, the final size should be 84 subjects in each group. The total sample size should be 168 subjects.

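### The group comparison in section 2.7 uses covariate-free tests although baseline values and age are recorded; it is valid but less precise than a baseline-adjusted model

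*Protocol article*

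**What the plan says.** Section 2.7 (Statistical Analysis) places the comparison of the two arms in a bivariate stage: "in the bivariate analysis a hypothesis test will be carried out". For a categorical factor such as group against a numerical outcome, it names Student's t or "ANOVA to compare qualitative with quantitative variables". For two categorical variables it names chi-square. If normality fails, the tests are "the Wilcoxon test, the Kruskal–Wallis test, and the Mann–Whitney test". Regression has a different role: "linear regression or Pearson correlation for the comparison of quantitative variables". No covariate is attached to the comparison between arms.

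Section 2.5 (Blinding and Monitoring) shows that baseline values will exist for the outcomes: "An initial assessment will be made, these same measurements will be repeated 3 times throughout the duration of the study". Section 2.4.2 lists age in months, and section 2.2 admits children from 3 to 12 years. The Introduction cites authors who place formation of the medial arch between 3–4 and 10 years of age. Section 2.1 describes an Excel-generated random sequence and mentions no stratification by age or severity.

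**The concern.** A child's own starting value is usually among the best predictors of the later value on the same scale. Over an age span in which the cited authors say the arch is still developing for most of the range, age is a plausible second predictor. A two-group test of follow-up values leaves the variation explained by both in the error term, so the confidence interval is wider than the collected data require. In a trial that expects to lose 30% of its children, that precision is worth having.

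**Working it through.** **Inputs.** From section 2.6: 64 per group before losses, 84 per group after allowing for 30% losses, 80% power, "a clinical variation of 2 and a standard deviation of 1 have been considered". From section 2.7: "The significance level of p shall be 0.05", taken as two-sided because sidedness is not stated. The correlation r between baseline and follow-up is in no section; the range 0.3 to 0.7 is an assumption.

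**1. The plan's own figure.** With the normal approximation, n per group = 2(1.96 + 0.84)² / d², where d is difference/SD.
- Stated inputs: d = 2/1 = 2.0 gives 4 per group (6 with the t distribution), not 64.
- d = 0.5 gives 63 per group (64 with the t distribution, power 0.801).

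So 64 per group corresponds to d = 0.5, and that value is used below. It is inferred from the sample size, not stated in the article.

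**2. Gain against a comparison of follow-up values.** Adjusting for baseline multiplies the residual variance by 1 − r², so the effective standardised difference becomes 0.5/√(1 − r²). At 64 per group:

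| r | variance factor 1 − r² | standard error ratio | effective d | power (t distribution) | power (normal approx.) |
|---|---|---|---|---|---|
| unadjusted | 1.00 | 1.00 | 0.50 | 0.801 | 0.807 |
| 0.3 | 0.91 | 0.954 | 0.52 | 0.837 | 0.843 |
| 0.5 | 0.75 | 0.866 | 0.58 | 0.900 | 0.904 |
| 0.7 | 0.51 | 0.714 | 0.70 | 0.976 | 0.977 |

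Expressed as sample size, 64 × (1 − r²) gives 59, 48 or 33 per group for the same power.

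**3. After the expected losses.** 84 × 0.70 = 58.8, taken as 58 per group. At d = 0.5 (normal approximation), power is 0.768 unadjusted and 0.806, 0.875 or 0.965 adjusted.

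**4. Gain against a comparison of changes.** A change score has variance factor 2(1 − r), against 1 − r² for ANCOVA. The difference is 2(1 − r) − (1 − r)(1 + r) = (1 − r)², which is never negative.
- r = 0.3: 1.40 against 0.91
- r = 0.5: 1.00 against 0.75
- r = 0.7: 0.60 against 0.51

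ANCOVA is therefore at least as efficient whichever form the plan intends.

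**5. With the stated d = 2.0.** Power at 64 per group is about 1.00 with or without adjustment. The narrower interval remains, but the power argument disappears.

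Any further gain from age cannot be computed from the article.

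**The case against.** The strongest reply is that nothing is invalid here. That stands: in a randomised trial an unadjusted t or rank test is unbiased over randomisation and holds its error rate. A reader might infer that chance baseline differences bias the result as a second, separate harm. They do shift the estimate in a given trial: at r = 0.5, a baseline difference of 0.25 SD moves it by 0.5 × 0.25 = 0.125 SD. But that variability is already inside the unadjusted standard error, so it is the same loss of precision seen from another side.

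A reader might also infer that the plan ignores baseline altogether. The article does not go that far. It does not say whether follow-up values or changes are tested, the Abstract expects improvement relative to the initial measurements, and ANOVA or Wilcoxon could be meant as repeated-measures or paired methods. This softens the point without removing it. No such use is stated, a change score is never more efficient than ANCOVA, and age would still be left out.

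Two further replies limit the size. The eligibility cut-offs in section 2.2 (Foot Posture Index, navicular drop, calcaneal stance position, pronation angle) narrow the baseline range, which may push r towards the lower end. And the developmental argument for age is reported from cited authors, with formation ending at 10; it is not the protocol's own claim about the whole 3-to-12 range.

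Finally, covariates are often left to a statistical analysis plan that is not shown. Here, though, section 2.7 does more than stay silent: it assigns the comparison of arms to a bivariate test and regression to another purpose.

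**Conclusion.** The point holds as a recommendation on efficiency. The stated comparison of arms is valid but less precise than the collected data allow. Against a follow-up comparison, adjustment for baseline would cut residual variance by 9% to 49% and the standard error by about 5% to 29%, on the assumption that r lies between 0.3 and 0.7, with the lower part of that range perhaps more likely. The power gain, from 80% to between 84% and 98% at 64 per group, also rests on a standardised difference of 0.5. A reader might infer from it that the trial is underpowered on its stated assumptions; section 2.6 does not support that, because its difference of 2 and SD of 1 give power near 1 under either analysis. The mismatch between those inputs and 64 per group is a separate matter.

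**What to change.** In section 2.7, replace the bivariate comparison of arms as follows.

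- **Quantitative outcomes:** a linear model (ANCOVA) of the follow-up value on group, the baseline value of the same measure and age in months. Report the adjusted mean difference with its 95% confidence interval. For clearly non-normal outcomes such as pain, use a robust or bootstrap interval, or add a rank-based sensitivity analysis.
- **Categorical outcomes:** logistic or ordinal regression on group and age, adding the baseline category only where it varies at entry. It cannot be used for the heel rise or windlass tests, because section 2.2 requires a negative result on both, so the covariate would be constant. State that the resulting odds ratio is conditional on the covariates.

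The cost is a short rewrite of section 2.7, a few degrees of freedom and a little more analysis work in software already planned. No additional data are needed.

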## Abstract

Pediatric flat foot (PFF) is a very frequent entity and a common concern for parents and health professionals. There is no established definition, diagnostic method, or clear treatment approach. There are multiple conservative and surgical treatments, the implantation of foot orthoses (FO) being the most used treatment. The evidence supporting FO is very thin. It is not clearly known what the effect of these is, nor when it is convenient to recommend them. The main objective of this protocol is to design a randomized controlled trial to determine if personalized FO, together with a specific exercise regimen, produce the same or better results regarding the signs and symptoms of PFF, compared to only specific exercises. In order to respond to the stated objectives, we have proposed a randomized controlled clinical trial, in which we intend to evaluate the efficacy of FO together with strengthening exercises, compared to a control group in which placebos will be implanted as FO treatment along with the same exercises as the experimental group. For this, four measurements will be taken throughout 18 months (pre-treatment, two during treatment and finally another post-treatment measurement). The combination of FO plus exercise is expected to improve the signs and symptoms (if present) of PFF compared to exercise alone and the placebo FO group. In addition, it is expected that in both conditions the biomechanics of the foot will improve compared to the initial measurements.

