Once the FO have been provided, after assessing that it adapts well to the foot and does not cause discomfort, the patient will be requested to come in at 6 months. In the event that there is any discomfort or irritation to the child’s skin, an appointment will be made to readjust or modify the FO (in this visit the variables will not be evaluated, only the FO will be fixed; if there are no problems, this visit will not be carried out).

#### 2.3.2. Group 2

The participants will have the same intervention described for group 1, with the difference that they will use a placebo FO. This will be constructed using flat 1 mm 65 shore Ethylene-vinyl acetate (EVA), which will be cut to the foot size of the child and covered with the same top cover as the FO Group 1 to visually prevent them from being distinguished.

The instruments necessary for the development of this study and the budget necessary to carry out this clinical trial are included in Appendix D.

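### No primary outcome or decisive visit is named and the sample size is tied to neither, so testing at 0.05 does not hold the risk of a false claim for orthoses at 5%

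*Protocol article*

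**What the plan says.** **Outcomes.** The Introduction states the aim in terms of signs and symptoms as a whole. Sections 2.4.1 and 2.4.2 list 14 categorical and 15 quantitative variables. None is called primary or main there or anywhere else. Pain, Foot Posture Index (FPI) and pressure platform each appear in both lists.

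**Sample size (2.6).** The inputs are a difference of 2 and an SD of 1, with "A statistical power of 80% and a significance level of" 0.05 and a "95% confidence level". The result is 64 per group, raised to 84 per group (168 in total) for 30% loss. The section does not say which variable the difference belongs to, in what unit, or at which visit.

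**Analysis (2.7).** "It is intended to compare the dependent variables with the independent ones", using t-test, ANOVA, chi-square, correlation or regression, or rank-based alternatives. The difference between control and experimental groups is tested bivariately, and "The significance level of p shall be 0.05".

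**Visits.** Section 2.5 has a baseline and three repeats, all of which feed the analysis: "The second measurement will be a month of treatment", then 6 months, "as well as the last one at 12 months". The abstract says "four measurements will be taken throughout 18 months (pre-treatment, two during treatment and finally another post-treatment measurement". Section 2.3 sets the follow-up appointment at 6 months, and section 2.3.1 says that once the orthoses are supplied "the patient will be requested to come in at 6 months".

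**The concern.** A 0.05 level controls error for one test. The trial's conclusion is not one test. Section 3 expects better results on signs and symptoms, and nothing in the plan says which variable, in which form, at which visit, decides that. Any favourable p-value among the listed outcomes could be offered as support.

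The sample-size section would normally reveal the intended primary outcome, but here it does not. It therefore cannot be checked whether 168 children are enough for the comparison that matters, because that comparison is not identified. Nor can a primary outcome be chosen credibly after the group results have been seen.

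The schedule inconsistency adds to this. A reader who supposed that the final visit was meant would find it placed differently in the abstract and in section 2.5.

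**Working it through.** **1. Does the sample size point to an outcome?** Per-arm size for two means, two-sided 0.05, 80% power: n = 2(1.960 + 0.842)² / (difference/SD)².
- Stated inputs, difference/SD = 2/1 = 2: n = 2 × 7.85 / 4 = 3.9, so 4 per arm (6 by t-test). The stated 64 is not reproduced.
- Difference/SD = 0.5: n = 2 × 7.85 / 0.25 = 62.8, so 63 (64 by t-test). The stated 64 fits this standardised effect.
- Loss step: 64 × 1.3 = 83.2, giving the stated 84. Dividing by the retained fraction gives 64/0.7 = 91.4, so 92.

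The arithmetic mismatch is a separate matter. What counts here is that neither version identifies a variable or a visit.

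**2. Counting the outcomes.**
- Categorical: 14, less gender, physical activity and Beighton, leaves 11.
- Quantitative: 15, less age, weight, height, BMI and foot size, leaves 10.
- Total 11 + 10 = 21, or 18 if pain, FPI and pressure platform are counted once each.
- Three follow-ups: 21 × 3 = 63 possible group comparisons.

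**3. Independent tests, no true effect.** The article does not state sidedness; two-sided is assumed.
- 21 tests: expected false positives 21 × 0.05 = 1.05. Any significant difference: 1 − 0.95²¹ = 0.66. One favouring orthoses: 1 − 0.975²¹ = 0.41.
- 63 tests: expected 63 × 0.05 = 3.15. Any: 1 − 0.95⁶³ = 0.96. Favouring orthoses: 1 − 0.975⁶³ = 0.80.

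The outcomes overlap and the visits repeat the same children, so the 63-test figures are upper bounds.

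**4. Correlated tests.** Multivariate-normal test statistics with no effect, 50,000 simulated trials per setting, 21 outcomes. The documents give no correlations. Those between outcomes (0 to 0.7) and between visits (0.5 to 0.8) are assumptions.

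| Correlation between outcomes | One visit: any | One visit: favours orthoses | Three visits: any | Three visits: favours orthoses |
|---|---|---|---|---|
| 0 | 0.66 | 0.41 | 0.89–0.94 | 0.66–0.75 |
| 0.3 | 0.55–0.56 | 0.29 | 0.81–0.88 | 0.46–0.54 |
| 0.5 | 0.43 | 0.21 | 0.67–0.77 | 0.35–0.42 |
| 0.7 | 0.29–0.30 | 0.15 | 0.49–0.60 | 0.25–0.31 |

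With 18 outcomes the overall ranges are 0.28–0.60 and 0.14–0.37 at one visit, and 0.47–0.91 and 0.24–0.69 over three. A single pre-specified two-sided test gives 0.05 and 0.025.

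**5. Schedule, side by side.**
- Abstract: four measurements over 18 months. Section 2.5: the last is at 12 months.
- Sections 2.3 and 2.3.1: next appointment at 6 months. Section 2.5: a measurement at one month.

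**The case against.** **The detail may sit in an unseen analysis plan.** This stands for the method of multiplicity adjustment: its absence from a condensed article is not a finding. It does not stand for the primary outcome and its time point. The protocol presents a completed sample-size calculation, and that calculation depends on both.

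**A reader might infer that a chance benefit is likely.** The documents do not support that across the board. The 29–66% at one visit counts differences in either direction, including those favouring the placebo insole. The chance of one favouring orthoses stays below one half at a single visit, and exceeds it over three visits only when correlation between outcomes is low. What stands is a risk several times the nominal rate: 0.15/0.025 = 6-fold at the lowest.

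**A reader might infer that every outcome is tested at every visit.** The text never says so. It follows only from putting together the four measurements for analysis in 2.5 and the unranked tests in 2.7. The three-visit figures are conditional on that reading.

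**A reader might treat section 2.1 and Table A1 as further visit contradictions.** Both are project calendars, not visit times per child, so a span to February 2025 does not by itself contradict a last visit at 12 months. The abstract's 18 months might be a loose reference to the same study period. Staggered entry does not fully explain the longer follow-up, since Table A1 marks recruitment in August 2023 only. The firm conflicts are the two listed at the end of the working.

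**The count is soft.** It is 18 or 21 depending on the double listings. The conclusion is the same for both.

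**Conclusion.** The concern holds in this form: no primary outcome or decisive visit is designated, the sample size is attached to no named outcome, unit or visit, and unranked outcomes are compared at 0.05. The 5% level therefore does not apply to the trial's overall conclusion about orthoses.

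The firmer estimate of size is the one-visit range, about 29–66% for any significant difference and 15–41% for one favouring orthoses. The three-visit range, about 49–94% and 25–75%, needs the added inference about repeated testing. Both rest on a count of 21 outcomes, two-sided tests, equal correlations chosen by assumption, and all outcomes treated as normal test statistics. The schedule inconsistency is real but limited to the abstract, 2.3, 2.3.1 and 2.5. It matters here because the decisive visit cannot be named until it is settled.

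**What to change.** Before any group data are seen:

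1. Name one outcome already collected, in one form, at one named visit as primary, tested at two-sided 0.05. The choice is the investigators'; FPI total score is only an example.
2. In 2.6, state the difference and SD for that outcome and restate the power that the planned 168 children give. This does not require more enrolment. As an illustration, at a standardised effect of 0.5 with 30% loss, 84 × 0.7 = 58.8 per arm gives about 77% power by t-test.
3. Treat all other outcomes and visits as secondary, reported as estimates with 95% confidence intervals and no significance claims, or Holm-adjusted. Keeping everything confirmatory would be costly: Bonferroni at 0.05/21 = 0.0024 needs about 121 per arm at a standardised effect of 0.5, and at 0.05/63 = 0.0008 about 141.
4. Use one form each of FPI and pain for inference.
5. Reconcile the abstract, 2.3, 2.3.1, 2.5 and Table A1 to one measurement schedule.

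Cost: protocol wording and no added data collection. The other outcomes lose confirmatory status, and the restated power may be less favourable than the stated 80%.
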